**Discussion:**

The TECNOB study aims to inform the evidence-based knowledge of how telemedicine may enhance the effectiveness of clinical interventions for weight loss and related type-2 diabetes, and which type of obese patients may benefit the most from such interventions. Broadly, the study aims also to have a effect on the theoretical model behind the traditional health care service, in favor of a change towards a new "health care everywhere" approach.

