For these reasons, we developed TECNOB (TEChnology for OBesity), a comprehensive two-phase stepped down program enhanced by telecare for the long-term treatment of obese people with type 2 diabetes seeking intervention for weight loss [27]. The core aspects of TECNOB are the hospital-based intensive treatment and the continuity of care at home using new information and communication technologies (ICT) such as internet and mobile phones. ICT-based approaches have already been shown to be helpful in weight loss and long-term maintenance [10,12,28-32], but much more work remains to be carried out in order to confirm these findings. Furthermore, very few studies have investigated the effects of an ICT-based program on obese patients with established type 2 diabetes and to our knowledge no study has tested a comprehensive long-term stepped down intervention starting with 1-month hospitalization specifically addressed to weight loss.

TECNOB protocol was mainly framed within the self-determination theoretical model of behavior change [33] and thus emphasizes the importance of maximizing the patients' experience of autonomy, competence and relatedness for the successful maintenance of behavior change [18].

This paper describes the design of the TECNOB study, a two-arm randomized controlled trial (RCT). The aims of this study are to evaluate the effectiveness of the TECNOB program in a sample of obese people with type 2 diabetes seeking treatment for weight reduction and to find out what behavioral and psychological variables are predictive of treatment success.

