
In addition to videoconference, outpatients can further contact clinicians by e-mail. Indeed, each patient is given the possibility to join his clinician beyond the established videoconference contacts in case of urgency or emergency. According to the e-message's content, clinicians choose the most appropriate format for delivering feedback among e-mail or telephone. In order to avoid excessive dependence and to contain costs, a maximum number of 1 not scheduled contact a week is established a priori.

As described, in the outpatient phase of the TECNOB program great relevance is given to the clinicians-patient relationship as an important medium and vehicle of change [18]. After discharge, out-patients begin to experience the autonomy and competence to change they develop during the in-patient phase and inevitably face resistances and barriers. Thanks to videoconferences, out-patients are supported by the clinicians who attended them during the in-hospital phase in exploring resistances and barriers they experience and in finding functional pathways to cope. Furthermore, out-patients are helped to experience mastery in terms of the health behavior change that needs to be engaged.

Participants in the control group will receive the hospital-based treatment and will be asked to respond to the follow-up assessments. No contact will be maintained with them at home and no continuous care will be provided after discharge.

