### Statistical analysis

Descriptive statistics (means ± SD, or median and interquartile ranges, as appropriate) will be used to describe the study sample with regard to baseline characteristics. Before selecting the most appropriate statistical tests, assumptions for parametric analyses will be checked. Repeated-measure ANCOVA will be used in order to evaluate the effects of the intervention when data do not violate the parametric assumptions. The mean differences between intervention and control group with 95% confidence intervals will be calculated. Analyses will be adjusted for possible confounders such as gender and age. Also effect modification will be investigated using interaction terms between intervention group and gender and age, respectively. If data violate parametric assumptions, we will use the exact methods with Monte Carlo approximation, a series of non-parametric statistical algorithms that enable researchers to make reliable inferences when data are sparse, heavily tied or unbalanced, not normally distributed, or fail to meet any of the underlying assumptions necessary for reliable results using the standard asymptotic method [50]. The Mann-Whitney test with Monte Carlo approximation will be used for independent measures, the Wilcoxon rank-sum test for repeated measures and the Fisher exact test for categorical variables. Weight data will be analyzed with an intention-to-treat (ITT) approach with dropouts assumed to have regained 0,3 kg per month, an assumption already used in previous studies [12,51]. Differently, missing data in the other variables will be replaced with baseline observation carried forward (BOCF) or last observation carried forward (LOCF) as appropriate, assuming no improvement for non-responders patients. Odds ratios with 95% confidence intervals will be also calculated at each follow-up time-point with respect to: 1) the percentage of participants maintaining or improving weight lost at discharge and 2) the percentage gaining a 5% and a 10% of baseline weight reduction for the TECNOB group in comparison with the control group. Finally, logistic regression will be used in order to find out predictors of treatment success defined as weight loss maintenance at the final follow-up time-point.

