## Discussion

The TECNOB program will be evaluated in a randomized controlled trial. We will test the effectiveness of this stepped down program enhanced by telecare on weight loss, weight loss maintenance, energy expenditure, glycated hemoglobin, binge eating, self-efficacy in eating and weight control, body satisfaction, healthy habit formation, disordered eating-related behaviors and cognitions, psychopathological symptoms and weight-related quality of life. Furthermore, we will explore the key behavioral and psychological variables predictive of treatment success and thus define the type of patients that benefit the most from such an intervention.

The theoretical approach behind the TECNOB program is to "move the healthcare where it really needs" using an advanced telemedicine web-platform and mobile phones to ensure the continuity of care at home. The core value of the program is overall the clinical use of mobile devices in the out-patients' everyday life. Indeed, the mobile connectivity can extend the treatment till the real-life environments of each patient, where traditional interventions typically fails because of the low compliance many obese patients have in carrying on with diet programs without active monitoring and support. Furthermore, mobile phones allow patients to receive "clinically oriented" SMS (such as food images indicating their day diet) that improve the reliability of the nutritional prescriptions. The results of this study will contribute to the evidence-based knowledge of how telemedicine may enhance the long-term efficacy of clinical interventions for weight loss and which type of obese patients may benefit the most from such an intervention. Results will also have an impact on the theoretical model behind the traditional health care service and, if positive, will promote a change towards a new "health care everywhere" approach.

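### Predictors of weight-loss maintenance are read as showing which patients TECNOB helps most, but arm interactions are planned only for gender and age

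*Protocol article*

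**What the plan says.** All references are to the protocol article.

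- **Aim, narrow form.** The Background sets out "to find out what behavioral and psychological variables are predictive of treatment success". The Methods paragraph of the Abstract says much the same.
- **Aim, wider form.** The Discussion paragraph of the Abstract wants to learn "which type of obese patients may benefit the most from such interventions". The main Discussion links the two forms: the study will explore "variables predictive of treatment success and thus define the type of patients that benefit the most from such an intervention".
- **Analysis of predictors.** Statistical analysis gives one sentence: "logistic regression will be used in order to find out predictors of treatment success defined as weight loss maintenance at the final follow-up time-point". It does not state the model terms, which arms enter, or the candidate variables.
- **Effect modification.** The same section says that "effect modification will be investigated using interaction terms between intervention group and gender and age, respectively". No behavioural or psychological variable is named there.
- **Comparator.** After discharge the control group receives no telecare: "No contact will be maintained with them at home and no continuous care will be provided after discharge" (Intervention).

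**The concern.** A variable that predicts success tells us who does well. It may raise the chance of keeping weight off by the same amount with or without telecare. To say that one type of patient benefits more from TECNOB, the difference between TECNOB and control must be shown to vary with that variable. This is an arm-by-variable interaction, and the plan names one only for gender and age. For the behavioural and psychological variables, which carry the wider aim, the only stated analysis is the logistic model of success, with no treatment interaction mentioned.

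If the Discussion's link is followed, prognostic factors would be reported as markers of benefit. Telecare might then be steered towards patients who would do well without it, while those it does help go unnoticed.

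**Working it through.** **Inputs.** From Sample size calculation: difference 3 kg, SD 6 (stated for control-group regain; taken here as kg and for both arms), alpha 0.05 two-sided, power 0.80, 64 per group, 154 in total after allowing for 20% dropout. From Statistical analysis: dropouts regain 0.3 kg per month. The odds ratios and the shares of patients with a characteristic are assumptions.

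**The plan's own figure.** n = 2 × (1.960 + 0.842)² × 6² / 3² = 2 × 7.85 × 4 = 62.8, so 63 per group. The t-test version gives 63.77, so 64. The plan's 64 is reproduced. The article gives no figure for the predictor analysis.

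**What each model can see.** 2,000 simulated trials of 154 patients (77 per arm) were run for each scenario, with one standardised score, logit intercept −0.4 and a log odds ratio of 0.7 for arm at the mean score. The main-effects model has arm and score; the interaction model adds arm × score. Each term is tested at 0.05.

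| Scenario | OR per SD, control | OR per SD, TECNOB | Ratio of ORs | Score flagged, main-effects model | Interaction flagged |
|---|---|---|---|---|---|
| Prognostic only | 2 | 2 | 2/2 = 1 | 98% | 4% |
| Pure modifier | 0.5 | 2 | 2/0.5 = 4 | 4% | 98% |
| Mixed | 1 | 2 | 2/1 = 2 | 48% | 49% |

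The TECNOB odds ratio is 2 in all three rows. A model fitted in TECNOB patients only would therefore estimate the same association whether modification is absent, moderate or strong. Without the control column the question cannot be answered. The first row has no interaction on the logit scale; on another scale the answer may differ, which is a further reason to name the scale and test the contrast directly.

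**Precision of an interaction in kg.** For a yes/no characteristic held by a share f of patients, with n per arm: SE = 6 × √{2 × [1/(nf) + 1/(n(1−f))]}; smallest difference detectable at 80% power = 2.80 × SE; power for 3 kg = Φ(3/SE − 1.96).

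| Patients | f | SE (kg) | Detectable (kg) | Power for 3 kg |
|---|---|---|---|---|
| 128 | 0.5 | 2.12 | 5.9 | 29% |
| 128 | 0.3 | 2.31 | 6.5 | 25% |
| 154 | 0.5 | 1.93 | 5.4 | 34% |
| 154 | 0.3 | 2.11 | 5.9 | 30% |

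First row in full: 6 × √{2 × (1/32 + 1/32)} = 6 × √0.125 = 2.12, and Φ(3/2.12 − 1.96) = Φ(−0.55) = 0.29. The 128 is 2 × 64, the plan's evaluable target. Taking 20% off 154 leaves 123 (61.6 per arm), so SE = 6 × √{2 × (2/30.8)} = 2.16 and power is Φ(−0.57), about 28%.

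**Dropout and the success outcome.** A patient with no weight after discharge is assigned 0.3 × 12 = +3.6 kg by month 12. That is a failure if success means no regain above discharge weight. At 20% dropout, at most 0.2 × 154 = 30.8, so 31 outcomes, would be touched by the rule.

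**The case against.** **The article does not say the model is main-effects only or that it pools the arms.** This is correct, and such detail may sit in a fuller plan. The point does not depend on it. The error lies in the Discussion's inference, and no fit without an arm contrast supports that inference.

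**The formal aim is only to find predictors of success.** This largely stands. The Background and the Abstract's Methods paragraph are narrow, and a logistic model serves them. The wider claim appears only in the two Discussion texts, so limiting those texts is an acceptable repair.

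**The work is described as exploratory.** This is true and it lowers the stakes, but exploratory status does not turn a prognostic estimate into an estimate of benefit.

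**The remedy is weak.** Also true. The detectable interaction of 5.9 kg is about twice the 3 kg design difference. Seven independent interaction tests at 0.05 would give a 1 − 0.95⁷ = 30% chance of at least one false positive. That argues for a short list and for intervals.

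A reader might infer more, and the article does not support it:

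- **Too many candidates.** The questionnaires yield 2 + 1 + 6 + 1 + 11 + 12 + 5 = 38 scores, so one could predict 38 × 0.05 = 1.9 false predictors and a 1 − 0.95³⁸ = 86% chance of at least one. Nothing says that all 38 are candidates, and global indices are not independent of their own subscales.
- **A trivial regain counts as failure.** The predictor sentence sets no threshold. The comparison with discharge weight comes from the separate odds-ratio sentence.
- **All dropouts become failures.** The article does not say which weight the monthly regain is added to. If it is the last observed weight, a patient 3 kg below discharge at month 6 who then leaves is assigned −3 + 6 × 0.3 = −1.2 kg and still succeeds.
- **The selected predictors would be mostly chance and dropout.** The number of true predictors is unknown, so this cannot be shown.

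**Conclusion.** The concern holds in a limited form. The article treats predictors of success as identifying who gains most from TECNOB. For the behavioural and psychological variables, its only stated analysis has no stated treatment interaction and so cannot show this, whichever arms are fitted.

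The 98% and 4% figures illustrate the direction of the error under assumed odds ratios and an assumed main-effects form; they do not predict this trial's results. The power figures rest on SD 6 in both arms, a yes/no characteristic, an assumed share and a normal approximation. Adjustment for baseline weight or use of a continuous score would change them somewhat.

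The dropout issue is a secondary caution: predictors of retention may appear as predictors of success, under the stated reading of success. The effect is moderate to low. It concerns an exploratory conclusion, and the confirmatory weight comparison is untouched.

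**What to change.** - Pre-name a short list of baseline behavioural and psychological scores, stating the exact score for each. EDI-2 and IWQOL-Lite are described by subscales only, and SRHI covers two behaviours, so naming the instrument is not enough. The Outcome Questionnaire is collected before videoconference sessions, which controls do not have, so it cannot be on the list.
- For each listed score, add an exploratory arm-by-score interaction to the model of 12-month weight, adjusted for baseline weight. Report the estimate with its 95% CI and say that precision is low.
- Describe the logistic regression as prognostic only.
- In the Abstract's Discussion paragraph and the main Discussion, limit statements about who benefits to variables whose interaction with arm is tested. If no interactions are added for the behavioural and psychological variables, keep for them only the narrow aim of predicting success.
- Add a sensitivity fit of the logistic model on observed or multiply imputed outcomes, to show how far the regain assumption for dropouts drives the predictors.

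The cost is wording and a few extra models. No new data are needed, because the listed questionnaires are completed at study entry and randomisation follows the baseline measurements. The drawback is wide intervals, which may leave the question of who benefits open.

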## Discussion

The TECNOB program will be evaluated in a randomized controlled trial. We will test the effectiveness of this stepped down program enhanced by telecare on weight loss, weight loss maintenance, energy expenditure, glycated hemoglobin, binge eating, self-efficacy in eating and weight control, body satisfaction, healthy habit formation, disordered eating-related behaviors and cognitions, psychopathological symptoms and weight-related quality of life. Furthermore, we will explore the key behavioral and psychological variables predictive of treatment success and thus define the type of patients that benefit the most from such an intervention.

The theoretical approach behind the TECNOB program is to "move the healthcare where it really needs" using an advanced telemedicine web-platform and mobile phones to ensure the continuity of care at home. The core value of the program is overall the clinical use of mobile devices in the out-patients' everyday life. Indeed, the mobile connectivity can extend the treatment till the real-life environments of each patient, where traditional interventions typically fails because of the low compliance many obese patients have in carrying on with diet programs without active monitoring and support. Furthermore, mobile phones allow patients to receive "clinically oriented" SMS (such as food images indicating their day diet) that improve the reliability of the nutritional prescriptions. The results of this study will contribute to the evidence-based knowledge of how telemedicine may enhance the long-term efficacy of clinical interventions for weight loss and which type of obese patients may benefit the most from such an intervention. Results will also have an impact on the theoretical model behind the traditional health care service and, if positive, will promote a change towards a new "health care everywhere" approach.
